## Abstract

**Background:**

Prostate cancer screening among the general population is highly debatable. Nevertheless, screening among high-risk groups is appealing. Prior data suggests that men carrying mutations in the BRCA1& 2 genes may be at increased risk of developing prostate cancer. Additionally, they appear to develop prostate cancer at a younger age and with a more aggressive course. However, prior studies did not systematically perform prostate biopsies and thus cannot determine the true prevalence of prostate cancer in this population.

**Methods:**

This will be a prospective diagnostic trial of screening for prostate cancer among men with genetic predisposition. The target population is males (40–70 year old) carrying a BRCA1 and/or BRCA2 germ line mutation. They will be identified via our Genetic counseling unit. All men after signing an informed consent will undergo the following tests: PSA, free to total PSA, MRI of prostate and prostate biopsy. The primary endpoint will be to estimate the prevalence, stage and grade of prostate cancer in this population. Additionally, the study aims to estimate the impact of these germ line mutations on benign prostatic hyperplasia. Furthermore, this study aims to create a bio-bank of tissue, urine and serum of this unique cohort for future investigations. Finally, this study will identify an inception cohort for future interventional studies of primary and secondary prevention.

**Discussion:**

The proposed research is highly translational and focuses not only on the clinical results, but on the future specimens that will be used to advance our understanding of prostate cancer patho-physiology. Most importantly, these high-risk germ-line mutation carriers are ideal candidates for primary and secondary prevention initiatives.

**Trial registration:**

ClinicalTrials.gov: NCT02053805.

## Background

### The prostate cancer screening debate

Prostate cancer is the most frequently diagnosed cancer and the second leading cause of cancer-related death among men
[1]. The most notable feature of prostate cancer diagnosis and staging in the last two decades was the shift from a disease that presented late, either as locally advanced or metastatic tumor, to one that is found in an earlier, often pre-clinical, stage
[2]. The exponential increase in the number of cases of early-stage disease has brought with it queries regarding the optimal method of treating these cases. We now question the necessity of diagnosing prostate cancer at an early stage, as earlier detection has not been convincingly associated with improved outcomes and may increase harm
[3-5].

This shift may be attributed mainly to the wide-scale use of prostate-specific antigen (PSA) as a screening tool and trans-rectal ultrasound (TRUS)-guided biopsy for diagnosis. At present, most patients with prostate cancer are detected by an elevated serum PSA, leading to trans-rectal biopsy
[1,2].

Recently, two large prospective randomized trials designed to test the hypothesis that PSA-based screening would reduce mortality were published. The European Randomized Study of Screening for Prostate Cancer (ERSPC) tested this in Europe
[6,7], and the Prostate, Lung Colorectal, and Ovary (PLCO) study
[8] tested it in the United States. The European study found that screening was associated with reduced prostate cancer–specific mortality compared with no screening in a subgroup of men aged 55 to 69 years after 9 years (relative risk, 0.80 [95% CI, 0.65 to 0.98]; absolute risk reduction, 0.07 percentage point). The PLCO study found no statistically significant effect after 10 years (relative risk, 1.1 [CI, 0.80 to 1.5]). One of the notable criticisms of the PLCO study is that up to 56% of men in the control arm underwent PSA screening compared with 15% in the European study.

The most common side effects associated with prostatic biopsies are hematospermia, hematuria, fever, hospitalization for prostatitis or urosepsis, and urinary retention
[9-11]. Whether the harms of screening are justified by the benefits, in terms of the reported reduction of prostate cancer mortality, is still a very controversial topic. Recently, the U.S. Preventive Service Task Force published a review of the evidence for screening for prostate cancer and made a grade D recommendation against it
[3]. On the contrary, the American Society of Clinical Oncology, the American Urological Association and Society of Urological Oncology all state that despite the limitations to the existing data, there is evidence to suggest that men with longer life expectancy may benefit from PSA testing
[4,5].

Given the ratio of prostate cancer incidence to prostate-cancer-related mortality, performing routine biopsies for all men would result in many healthy men being labeled as patients unnecessarily. Thus, identifying men at elevated risk of developing potentially life-threatening prostate cancer is a necessity. Men with germ line genetic mutations may represent such a high risk group.

### Genetics and prostate cancer

The pathogenesis of prostate cancer is complex and multifactorial. Consequently, only a limited number of important risk factors for prostate cancer are well accepted. In general, the risk of prostate cancer is increased by African ethnicity, increasing age, and family history. As with other cancers, familial clustering of prostate cancer has been reported. It is now estimated that 5% to 10% of prostate cancer cases are due primarily to high-risk inherited genetic factors or prostate cancer susceptibility genes
[12]. Genetic studies suggest seven potential genes are involved in Hereditary Prostate Cancer. Three of these are located on chromosome 1 (HPC1, PCAP and CAPB) and the other four are located on chromosome 17 (HPC2), chromosome 20 (HPC20), chromosome 8 and the X chromosome (HPCX)
[13-17]. However, no single susceptible gene is, by itself, responsible for a large portion of familial prostate cancers.

There are also several genetic conditions associated with an increased risk of prostate cancer. Hereditary breast and ovarian cancer (HBOC) syndrome and Lynch syndrome are the most common ones. HBOC is associated with mutations in the BRCA1 and/or BRCA2 (BRCA stands for BReast CAncer). HBOC is most commonly associated with an increased risk of breast and ovarian cancer in women. However, men with HBOC also have an increased risk of breast cancer and prostate cancer
[12].

### BRCA and prostate cancer

BRCA1 and BRCA2 are tumor suppressor genes. In normal cells, BRCA1 and BRCA2 help ensure DNA stability and help prevent uncontrolled cell growth. Genetic instability is a characteristic of BRCA1/2 deficient cells that leads to an accumulation of genomic and post genomic abnormalities. Mutations of these genes are linked to the development of HBOC. However, these genetic mutations do not affect only woman. Several studies have reported that the risk of prostate cancer is higher among men carriers of both BRCA 1 and 2
[15-20]. The results from the Breast Cancer Linkage Consortium (BCLC) showed a RR of 4.65 of prostate cancer in male BRCA2 mutation carriers (RR 7.33 below the age of 65 years) and 1.07 in BRCA1 carriers (with a RR of 1.82 for men under 65 years old)
[21,22]. Recent studies have suggested that the risk for male BRCA1 mutation carriers may be lower than previous estimates and that BRCA2 mutation carriers may have a significantly higher RR of 23-fold at age 60
[23,24]. Furthermore, BRCA mutations may be linked not only to susceptibility to prostate cancer, but also to the aggressiveness of the disease
[17-20].

The largest study to date was recently published at JCO
[20]. This study analyzed the tumor features and outcomes of 2,019 patients with prostate cancer (18 BRCA1 carriers, 61 BRCA2 carriers, and 1,940 non-carriers). Germline BRCA1/2 mutations were associated with higher grade, stage, nodal involvement and metastasis at diagnosis. Prostate specific survival was significantly longer among non-carriers compared to BRCA carriers (15.7 v 8.6 years). Subgroup analyses confirmed the poor outcomes in BRCA2 patients, whereas the role of BRCA1 was not well defined due to the limited size and follow-up in this subgroup.

To summarize, prostate cancer tends to be an indolent cancer mainly affecting older men. However, individuals carrying germline mutations such as BRCA 1/2 are not only at increased risk of developing prostate cancer, but there is evidence suggesting that this high-risk group may develop prostate cancer at a younger age with a more aggressive phenotype. Clearly, in these subjects there is a role for a personalized screening approach.

### Objectives

The purpose of this study is to:

1) Determine the prevalence and severity of prostate cancer among BRCA carriers.

2) Determine the accuracy and cost-effectiveness of different screening options for prostate cancer in this group (PSA, free to total PSA, prostate MRI).

3) Determine the prevalence and severity of benign prostatic hypertrophy and lower urinary tract symptoms among this group.

4) Establish a biobank of this unique population.

## Methods/design

### Study design

This is a prospective diagnostic trial of screening for prostate cancer among men with high genetic predisposition (BRCA1\2) to estimate the incidence of prostate cancer, and the accuracy and cost effectiveness of different screening modalities in this population. Additionally, this study aims to estimate the impact of these germline mutations on BPH and LUTS. Furthermore, this study aims to create a bio-bank of tissue, urine, and serum of this unique cohort for future investigations. Finally, this study will identify an inception cohort for future interventional studies of primary and secondary prevention.

### Study population

The target population is males carrying germline mutations in BRCA1 or BRCA2. Eligible men, carriers of one or more of the above mentioned mutations, will be identified through collaboration and under supervision of the genetic clinic in Beilinson hospital.

Individuals expressing interest in taking part in the study will be contacted by the research team and an initial appointment will be scheduled. The individual will be given the option to participate in the MRI and the prostatic biopsy. Fully informed written consent will be sought before collecting any research samples.

Inclusion criteria

• Male carrier of mutation in BRCA 1\2.

• Age 40–70 years.

• WHO performance status 0–2 (Additional file
1).

• No previous history of prostate cancer.

• No previous prostate biopsy.

• Absence of any psychological, familial, sociological or geographical situation potentially hampering compliance with the study protocol and follow-up schedule.

• Individuals that cannot undergo the MRI exam due to high creatinine level or claustrophobia will be excluded from the MRI part.

• Informed written consent must be sought according to ICH/EU GCP, before subject I inclusion.

Exclusion criteria

• Previous cancer with a terminal prognosis of less than five years.

• Previous prostate cancer.

### Primary endpoint

To determine the prevalence, stage, and pathology of screen-detected prostate cancer in BRCA1/BRCA2 founder mutation carriers.

### Secondary endpoints

1. To test the accuracy (sensitivity, specificity, positive and negative predictive value) of different screening tests (PSA, free to total PSA, prostate MRI) in detecting prostate cancer among men with genetic predispositions.

2. To test the accuracy (sensitivity, specificity, positive and negative predictive value) of different screening tests (PSA, free to total PSA, prostate MRI) in detecting clinically significant prostate cancer among men with genetic predispositions.

3. To establish the cost effectiveness of different screening tests (PSA, free to total PSA, prostate MRI) in detecting prostate cancer and clinically significant prostate cancer among men with genetic predispositions.

4. To determine the impact of these genetic mutations on lower urinary tract symptoms (International Prostate Symptoms Score - IPSS, flow and post void urine residual) and BPH (trans-rectal US prostate size).

5. To characterize the genomic and biological profiles in samples from these mutation carriers and characterize changes related to prostate cancer.

### Study procedures

The study flowchart is presented in Figure 
1; study timeline is presented in Additional file
2.

**Figure 1 F1:**
[figure not shown]
CONSORT diagram.

#### First round of screening

The following investigations will be performed in the first visit after informed consent was obtained.

1. Each patient will provide 50 ml blood sample for PSA and free to total PSA tests. The serum will be stored for future investigations.

2. Each patient will be asked to complete the IPSS questionnaire - a validated lower urinary tract symptom questionnaire (Additional file
3).

3. DRE followed by a urine sample will be provided for storage (Additional file
4). Creatinine level will be checked.

4. Each patient’s urinary flow and post void residual will be measured. The post void residual will be recorded by using ultrasound.

5. Subjects will undergo a multi-parametric prostate MRI using the Ingenia 3.0Tesla with the following protocol:

• Axial, T2-weighted and T1-weighted turbo spin echo imaging will be performed over the pelvic region. 40 slices acquired with a thickness/gap of 5.0/1.0 mm, FOV AP 300 mm × RL 300 mm × FH 239 mm. For the T2-weighted scan, a SPAIR adiabatic fat suppression will be applied. The TR/TE 3800/80ms, the acquisition matrix 272 × 209, turbo factor 19, NEX = 1 and the SENSE parallel imaging factor 2.0 for an imaging time of 2:17 min. For the T1-weighted scan, the TR/TE s 567/8.0 ms, the acquisition matrix 332 × 288, turbo factor 8, NEX = 1 and the SENSE parallel imaging factor 2.0 for an imaging time of 2:57 min.

• For prostate imaging, T2-weighted turbo spin-echo images obtained in three orthogonal planes (axial, sagittal and coronal). The TE 120 ms, and the TR set the shortest possible (4000 – 6000 ms). The remaining scan parameters of T2-weighted images are presented in Table 
1.

**Table 1 T1:** Additional scan parameters of T2-weighted images

**Slice Direction**	**No. of slices**	**Slice width/gap (mm)**	**Turbo factor**	**FOV mm**		**Nex**	**Acq matrix**	**WFS (pixels)**	**Scan time (min)**
				**AP**	**RL**				
Axial	30	2.5/0.25	24	160	160	1	268 × 219	1.5	3:20
Coronal	20	3.0/0.3	26	180	180	2	300 × 248	1.0	4:40
Sagittal	20	3.0/1.0	26	180	180	2	300 × 252	1.0	4:17

6. An attempt will be made to collect at least a minimum core length of 1 centimeter on each biopsy core, when possible, in order to allow for a complete analysis. It is recognized that in some areas of the prostate this may be difficult but it is encouraged to obtain as long a core as possible. Cores with any amount of prostate tissue are counted as part of the 12-core schema. If no tissue is obtained in a biopsy core, the core may be repeated. In the event of a focal lesion on MRI, we will continue to follow the biopsy diagram for core sample location and if the focal lesion is not part of the standard 12-cores, we will obtain an additional sample of the focal lesion using MRI-US fusion system
[25,26]. The location of the biopsies will be labeled and sent to pathology. A single dedicated Uro-pathologist will review all pathological specimens.

The reason to offer all subjects a prostate biopsy irrespective of their PSA is that there is very limited evidence that PSA screening is useful among patients with BRCA mutations. Furthermore, results from the PCPT trial, which offered prostate biopsy to all subjects (independent of their PSA level), demonstrated that as many as 15% of men with a PSA value less than 3.0 ng/mL had prostate cancer and that 15% of these cancers were high grade. These results may be even more pronounced in a population of high- risk men with germline mutations. Moreover, data is accumulating that prostate cancer may be more aggressive among this subset of patients. Finally, the risk of serious side effects from prostate biopsies is minimal among a young and healthy population. We therefore believe that prostate biopsies are essential.

7. After results of the PSA, MRI, and pathology are available a visit will be scheduled with an urologist to determine further follow-up or treatment. If the biopsy is normal subjects will enter an annual PSA-based screening (for the first 5 years). If High Grade PIN is identified at biopsy, it is recommended that the biopsy is repeated after 6 months. If Atypical Small Acinar Proliferation (ASAP) is identified at biopsy, it is recommended that the biopsy is repeated after 3 months. The urologist will also review the results of the LUTS assessment and will offer an individualized treatment or follow up.

#### On annual review

Medical and family history will be updated, and then each subject will undergo PSA testing, and plasma and urine storage (Additional file
4). A decision to repeat prostate biopsy will be made based on clinical grounds (i.e. an abnormal PSA measurement)

#### If prostate cancer is diagnosed

The staging and further investigation of the disease is directed by the uro-oncology unit. Management is based on the pathology information and discussion between the Uro-oncologist and patient.

The following information will be recorded:

• Clinical T stage.

• Gleason grade of biopsy (primary and secondary).

• Volume of cancer on biopsy (i.e. the number of cores involved and percent of each involved core).

• Treatment and management plan (i.e. active surveillance, surgery, or radiation).

• Radiological TNM stage- if clinically appropriate results of CT scan + bone scan.

• Histopathology report.

• Annual follow-up will be offered to patients after prostate cancer diagnosis regardless of treatment center (we realize that not all patients will receive treatment at Rabin Medical Center).

• Progression, for those choosing active surveillance, and Biochemical recurrence rate, for those choosing surgery or radiation, will be monitored.

• Survival will also be monitored, but the number of prostate cancer deaths is unlikely to be sufficient for statistical analysis.

### Potential adverse events

As detailed earlier, we believe that a transrectal ultrasound and biopsy should be carried out on all subjects. This procedure will be done under local anesthesia; however, it is uncomfortable and associated with the following risks:

• Painful or difficult voiding- this may appear in 13% of patients, and usually lasts several hours.

• Hematuria- this is usually minimal, and may appear in 11% of patients and last for several hours.

• Septicemia- this is the most serious potential adverse effect. It may appear between 0.5-3% of patients. It usually occurs following repeated biopsies and among immune suppressed or older subjects. The target population in our study is young and non-had prior prostate biopsy (see inclusion/exclusion criteria). We therefore expect a low rate of septicemia. However, we will administer prophylactic Abx, as per protocol, and will ask any subject with fever or chills after the procedure to seek medical attention immediately.

• Acute urinary retention – this is very rare (0.1-1% of patients), and usually occurs among elderly subjects
[9-11].

For this reason, subjects will be followed carefully and be able to contact the urology department in case of problems.

### Removal from the study

Subjects may withdraw from the study at any time, if they so wish, without giving a reason. Data will be censored for participants who develop prostate cancer or are too unwell to attend screening.

### Statistics

#### Primary analysis

The primary aim of this study is to estimate the true prevalence of prostate cancer among men with genetic predisposition. Since our study will offer a prostate biopsy to all subjects upon entry we will avoid “verification bias” associated with PSA based screening. However, this fact prevents us from including a control group, as we feel it may be unethical to offer non-carrier such a work-up. Therefore, we will use descriptive statistics only to report the primary outcome stratified by mutation. The fact that we are not including a control group also prevents us from providing a sample size calculation. We will perform a preliminary analysis of our data after 220 patients.

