### Secondary analysis

1. Descriptive statistics stratified by mutation will be used to report stage and grade of prostate cancer.

2. Sensitivity, specificity, positive and negative predictive value of: PSA, free to total PSA, prostate MRI in detecting prostate cancer among men with genetic predispositions will be calculated.

3. A Receiver Operating Curve (ROC), and calibration and decision curve analyses will be performed for each of the aforementioned screening tests. The threshold for biopsy for each test will be calculated based on any prostate cancer detected as well as clinically significant cancer detected (for the purpose of this study any cancer with a Gleason sum equal or higher than 7 will be considered clinically significant).

4. We will use a Markov model to establish the cost effectiveness of different screening tests (PSA, free to total PSA, prostate MRI) in detecting prostate cancer and clinically significant prostate cancer among men with genetic predispositions.

5. Descriptive statistics stratified by mutation will be used to report the impact of these genetic mutations on lower urinary tract symptoms (IPSS, flow and post void urine residual) and BPH (trans-rectal US prostate size).

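### Carriers-only data cannot show the mutations' impact on LUTS and BPH, and comparisons between mutations need age-standardised or age-adjusted figures beside the crude ones

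*Protocol article*

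**What the plan says.** **LUTS and BPH.** Secondary endpoints, item 4, reads "To determine the impact of these genetic mutations on lower urinary tract symptoms" and adds BPH, measured by transrectal ultrasound size. Secondary analysis, item 5, answers it: "Descriptive statistics stratified by mutation will be used to report the impact of these genetic mutations on lower urinary tract symptoms". The Study design section and the Methods paragraph of the Abstract also set out to estimate an impact (the Abstract for BPH only). Objectives, item 3, asks for something different: "Determine the prevalence and severity of benign prostatic hypertrophy and lower urinary tract symptoms among this group".

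**Comparator.** Study population admits only mutation carriers. Primary analysis gives the reason for having no controls: offering a biopsy to every man means that "this fact prevents us from including a control group, as we feel it may be unethical to offer non-carrier such a work-up".

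**Age and mutation.** Eligibility is "Age 40–70 years". For the primary outcome, "we will use descriptive statistics only to report the primary outcome stratified by mutation". Stage and grade (Secondary analysis, item 1) and LUTS/BPH (item 5) are likewise descriptive by mutation. The Background section on genetics states that "the risk of prostate cancer is increased by African ethnicity, increasing age, and family history". The Discussion claims sufficient power to find differences in prostate cancer parameters among the three founder mutations.

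**The concern.** There are two separate issues.

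1. The impact of a mutation is a contrast with men who lack it. If a secondary endpoint promises that contrast and the design contains no such men, a descriptive table of carriers may be read as evidence that the mutations do, or do not, affect urinary symptoms or prostate size.

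2. Cancer prevalence depends on age, and the eligible range spans 30 years. If the mutation groups differ in age mix, crude figures set side by side could show an age difference as a mutation difference, or hide a real one. This matters because the Discussion looks forward to exactly that comparison.

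**Working it through.** **Part 1: what carriers-only data identify.** Let the mean of an outcome (say IPSS) be m in comparable non-carriers, and m + d1, m + d2, m + d3 in carriers of the three founder mutations. The impact of each mutation is d1, d2 or d3. The study observes three means: m + d1, m + d2 and m + d3. That is three equations in four unknowns. Differences such as d1 − d2 can be estimated; no single d can. If every mutation raised IPSS by the same amount, all between-mutation differences would be zero although the impact was not. Objectives item 3 needs only the carrier means and frequencies, which are observed.

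The ethical reason for having no controls concerns the full work-up with biopsy. It does not by itself explain the lack of a comparator for IPSS, flow and post-void residual, which need no biopsy.

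**Part 2: how much an age imbalance could matter.** The article gives no prevalence by age and no age distribution by mutation, so there is no stated figure to reproduce. Everything below is assumed, for illustration, with the same age-specific prevalence in both groups (no true mutation effect).

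Crude prevalence = sum over bands 40–49, 50–59, 60–70 of (share in band × prevalence in band).

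Taking 5/15/25% by band:
- Mix 45/35/20: 0.45×0.05 + 0.35×0.15 + 0.20×0.25 = 12.5%.
- Mix 20/35/45: 0.20×0.05 + 0.35×0.15 + 0.45×0.25 = 17.5%. Ratio 17.5/12.5 = 1.40.
- Milder, 40/35/25 against 30/35/35: 13.5% and 15.5%. Ratio 1.15.

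Other assumed prevalences:

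| Prevalence by band | Age mixes compared | Crude prevalence | Ratio |
|---|---|---|---|
| 3/8/16% | 40/33/27 vs 27/33/40 | 8.2% vs 9.8% | 1.21 |
| 3/8/16% | 50/30/20 vs 20/30/50 | 7.1% vs 11.0% | 1.55 |
| 5/12/25% | 40/33/27 vs 27/33/40 | 12.7% vs 15.3% | 1.20 |
| 5/12/25% | 50/30/20 vs 20/30/50 | 11.1% vs 17.1% | 1.54 |
| either | equal mixes | equal | 1.00 |

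**Does standardising remove it?** In the 1.40 example with equal group sizes, the pooled mix is 32.5/35/32.5. Applied to either group it gives 0.325×0.05 + 0.35×0.15 + 0.325×0.25 = 15.0%, so the ratio returns to 1.00.

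**How large are these imbalances?** With band midpoints 45, 55 and 65, the mixes 45/35/20 and 20/35/45 have mean ages 52.5 and 57.5, a gap of 5 years; the milder pair differs by 2 years. If age were uniform on 40–70 (SD 30/√12 = 8.66) and groups differed only by chance, the 95% range for the difference in means is ±1.96 × 8.66 × √(2/n). That is ±2.3 years at n = 110 and ±2.8 years at n = 73 per group (220 men split in two or three). The milder gap could arise by chance; a 5-year gap would need something systematic, such as how men come to attention or survive to enrolment.

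**Against sampling error.** Near 15% prevalence, the 95% half-width for a difference is 1.96 × √(2 × 0.15 × 0.85/n): 9.4 points at n = 110 and 11.6 at n = 73. The assumed shifts of 2 to 5 points lie inside that.

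**The case against.** The strongest reply is aimed at the age part. A journal article condenses the full protocol, and age tables or covariates are commonly left to the analysis plan, so their absence here is not an error. The primary aim is to estimate prevalence, and crude prevalence by mutation is a valid description of the men studied. The Statistics section announces no contrast or test between mutations. All of that stands.

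A reader might infer that mutation differences in this study *are* confounded by age. The documents do not support that. Confounding requires age to differ between mutation groups, and no ages by mutation are given. Nor does the text say that men are recruited through families; it says they are identified through one genetic clinic, under one set of criteria. The cited BRCA2 relative risks (4.65 overall, 7.33 below 65) suggest that the effect varies with age; they do not show that ages differ between groups. The spurious ratios above are illustrations, and the shifts are small beside sampling error at about 220 men.

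What the reply does not remove is the Discussion's expectation of detecting differences between mutations, set against a primary analysis confined to descriptive statistics with one stratifier.

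On LUTS/BPH the only reply is that this is loose wording of a secondary endpoint, already worded properly under Objectives and limited to descriptives in the analysis. That bears on how serious the point is. The promise appears in four places, and unseen analysis detail would not remove it while the study enrols carriers only.

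**Conclusion.** The LUTS/BPH point holds firmly and rests on the article's own text: the impact of carrying a mutation cannot be estimated without non-carriers, and the endpoint and analysis wording disagree with Objectives item 3.

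The age point holds in a limited form. Any comparison between mutations *may* be confounded by age. If age mixes match, the bias is nil. Under the assumed prevalences and mixes, the spurious crude ratio is about 1.15 to 1.55, or 1.6 to 6 percentage points. Crude prevalence by mutation remains sound as the primary descriptive result; age limits how it can be compared, not whether it can be reported. Nothing here invalidates the study. It is a change worth making before results are reported.

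**What to change.** 1. In the Abstract, Study design, Secondary endpoints item 4 and Secondary analysis item 5, replace the impact wording with prevalence and severity of LUTS and BPH in carriers, and age-adjusted differences between mutations. The alternative is to name a comparator, for example an external or non-biopsied group for IPSS, flow and residual.
2. Keep crude cancer prevalence by mutation as the primary descriptive result. Beside it, give prevalence by mutation directly standardised to the whole cohort's age distribution, with the age distribution in each mutation group.
3. Adjust any contrast between mutations for continuous age and give 95% confidence intervals: logistic regression for cancer (penalised if cancers are few), linear regression for IPSS, flow, residual and prostate size. Such a model assumes the mutation contrast is constant over age; given the age-dependent relative risks in the Background, say so when reporting it.

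**Cost.** Age is known for every man because it is an eligibility criterion, so no new data are needed unless a comparator is added. The price is some extra analysis and limited precision. Three mutations by three age bands in 220 men is about 220/9 = 24 men per cell, or about 4 cancers per cell at an assumed 15% prevalence. Banded figures would therefore be very imprecise, which is why continuous age is preferable for the contrasts.
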